
### Schedule of the study

Step 1 is accessible since October 1st 2014. Step 2 is accessible since February 1st 2015 and Step 3 is accessible since March 1st 2015. All questionnaires will be accessible through December 31st 2015. Analysis and interpretation will be taking place subsequently to the study.

### Study centers

Data of all steps of the NURMI Study will be collected and analyzed in Austria. Core region are German-speaking countries of Europe (Germany, Austria, Switzerland).

### Ethical principles

The study is conducted in accordance with medical professional codex and the Helsinki Declaration as of 1996 as well as Data Security Laws and good clinical practice guidelines. Study participation is voluntary and can be cancelled at any time without provision of reasons and without negative consequences.

#### The subject’s written informed consent

Previous to study, subjects participating in the NURMI Study give written information about the content and extent of the planned procedure of the study. In case of study discontinuation, all data sets will be deleted.

#### Vote of the ethics committee

The study protocol was approved by the ethics board of St. Gallen, Switzerland on May 6, 2015 (EKSG 14/145).

#### Duties on the part of the investigators

The authors hereby confirm that ethical and scientific criteria as well as quality standards in terms of planning, study procedure, monitoring, analysis and documentation of the study will be fully observed and carried out in accordance with the protocol. All rights of the subjects will be respected and the results of the study will be handled correctly. The investigators are bound to conduct the study according to the study protocol and to report and document deviations to the ethics committee.

#### Evaluation of the risk–benefit ratio

All planned measurements are routine, justifiable and reasonable from a medical point of view. Study participation implicates no additional risk for the subject. Participation is voluntary and discontinuation will be possible at any time and without negative consequences. The study will be considered a contribution for endurance athletes, in particular endurance runners following some kind of vegetarian diet including the vegan diet. Moreover, the study aims to add knowledge to the currently very limited body of science considering the vegetarian but specifically the vegan endurance athlete. Furthermore the study could help to eliminate remaining concerns of coaches and runners and has the potential to show the adequacy of vegetarian and vegan diets on running performance as seen in professional runners.

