There are many vegetarian and vegan athletes especially in endurance and ultra-endurance disciplines such as Alan Murray and Janette Murray-Wakelin (marathon running) (Murray and Murray-Wakelin 2015), Michael Arnstein (marathon running) (Arnstein 2015), Fiona Oakes (marathon running), Vlad Ixel (ultra-marathon running), Scott Jurek (ultra-marathon running), Ruth Heidrich (triathlon) (Greatveganathletes.com 2015), Emil Voigt (Olympic track and field), Edwin Moses (Olympic track and field), Paavo Nurmi (Olympic track and field) (Finn 2015), Brendan Brazier (triathlon) (Braizer 2015), and Arnold Wiegand (ultra-triathlon) (Wiegand 2015).

Considering these and numerous other successful (ultra-) endurance athletes adhering to various vegetarian and vegan diets provides sufficient evidence that high-level endurance and ultra-endurance performance can be achieved by following a vegetarian or vegan diet. Therefore it is reasonable to conclude that a vegetarian or vegan diet is compatible with successful endurance and ultra-endurance performance. Yet the prevalence of vegetarians or vegans in endurance running events has not been investigated to date.

Scientific data about endurance and ultra-endurance athletes following a vegan diet is limited. Only two case reports describing vegan diet and athletic performance can actually be found in PubMed database (MEDLINE Database 2015). Wirnitzer and Kornexl (2014) described the successful implementation of a vegan diet during an 8-day mountain bike race of a female athlete. Leischik and Spelsberg (2014) investigated an ultra-endurance triathlete on a raw vegan diet, with reference to his ability to perform, cardiac status, and any symptoms of deficiency.

Since case reports are not adequate to draw any scientific conclusions to a larger population, the NURMI Study was designed as a comparative study with a large study population to investigate the prevalence in running events and to detect potential differences in running performance comparing three subgroups: omnivorous, vegetarian and vegan endurance runners.

The future results of the NURMI Study might be useful to develop adequate strategies on nutrition behavior and might help to design individualized interventions in order to meet the nutritional challenges of demanding endurance running races and the requirements of vegetarian and vegan endurance runners.

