### Trial objectives

The first and major goal of the NURMI Study is to compare endurance performance of vegetarian and vegan runners to non-vegetarian marathon runners and to determine potential differences/to identify possible correlations.The second goal is to investigate the prevalence of vegetarian and vegan runners in endurance (half-marathon and marathon) events.The third goal is to validate the subjects self-reports on his/her dietary behavior.

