### Strengths of the study

Since scientific data about endurance and ultra-endurance athletes following a vegan diet is limited the NURMI Study will be the first study to assess this issue considering a bigger sample size. The NURMI Study aims to provide a large data set comparing respective subgroups of omnivorous, vegetarian and vegan runners ranging from epidemiological aspects, dietary and training habits, in-race dietary consumption, and performance measurements. Large numbers of participants will allow to discriminate between and, identify associations with, different dietary patterns and level of training status as well as to detect differences in running performance between subgroups of omnivores, vegetarians and vegans. To make sure to assess fit runners only the NURMI Study focuses on runners who are at least capable of coping the half-marathon distance as the primary inclusion criteria.

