### Statistical methods

Analyses will be performed using commercially available software (IBM SPSS Statistics 23, SPSS Inc., Chicago, IL, USA). All data derived from the statistical methods will be given in mean ± standard deviation. Research shows that the most successful athletes in marathon and ultra-marathon running events are frequently those who lose substantially more than 3–4 % BW during competition (Zouhal et al. 2011). Mean body weight of male recreational marathon runners is 73.9 ± 8.1 kg (Barandun et al. 2012) and 75.8 ± 8.6 kg (Friedrich et al. 2014) of male recreational half marathon runners. Mean body weight of female recreational runners is 59.1 ± 6.3 kg (Rüst et al. 2013) and 60.1 ± 7.8 kg (Friedrich et al. 2014) of female recreational half marathon runners. Expected body weight loss during a marathon race is 2.3 ± 2.2 % overall (Zouhal et al. 2011). For male recreational marathon runners we expect a 2.3 % weight loss from 73.9 to 72.2 kg, therefore a sample size of 179 runners is needed to reach 80 % power with two-sided test and alpha of 0.05. For female recreational marathon runners we expect a 2.3 % weight loss from 59.1 to 57.7 kg, therefore a sample size of 159 runners is needed to reach 80 % power with two-sided test and alpha of 0.05. Since body weight loss during a marathon is inversely related to race finishing time (Zouhal et al. 2011) we expect the fastest runners to lose the most relative body weight during competition. Multi-variant regression analyses will be used the determine effects of kind of diet, sex, age, BMI, finished running distances, years of race experience, weekly training load, weekly training frequency, training intensity, in-race food and fluid consumption on individual finishing time (% of overall winners time, ranking, calculated pace). An analysis of variance will be performed to compare individual finishing time (% of overall winners time, ranking, calculated pace), sex, age, body weight, height, BMI, attended running events in past 2 years, finished running distances, personal best time on each distance, number of planned events for 2014/2015, daily/weekly training frequency, daily/weekly training load, period of preparation for main event, aim of race participation, years of running experience, motivation for running then and now, assisted training, years of race experience, training intensity, medium/long-term goal of racing, additional specific kinds of training, specific diet including supplements, specific training/diet prior to race, diet on day of rest/training/race, pre/in/post-race diet, in-race food and fluid consumption, specific gear, relevant medical measures, pre/post-race body weight (including clothing and shoes), calculated weight loss, in-race: nutritional strategy during race, fluid and nutrient intake including breakfast, mood status, and RPE (Borg) whole body/respiratory/legs, among the three subgroups created respective to diet.

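### The protocol offers showing the adequacy of vegetarian and vegan diets as a benefit, but it plans only tests for a difference, and a non-significant result from these could not support that claim

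*Protocol article*

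**What the plan says.** Adequacy appears once in the protocol article. Under Evaluation of the risk–benefit ratio, the study "has the potential to show the adequacy of vegetarian and vegan diets on running performance as seen in professional runners", and the same sentence says that it could help remove the doubts of coaches and runners.

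The aims and analyses are worded differently:

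- Trial objectives: the first goal is to "compare endurance performance of vegetarian and vegan runners to non-vegetarian marathon runners and to determine potential differences".
- Background: the study was designed "to detect potential differences in running performance comparing three subgroups".
- Statistical methods: "Multi-variant regression analyses will be used the determine effects of kind of diet" and other covariates on finishing time, and "An analysis of variance will be performed to compare individual finishing time" and many other variables across the three diet groups.
- Statistical methods also says that results will be given as mean ± standard deviation. No confidence interval, equivalence or non-inferiority hypothesis, or tolerated difference is mentioned.
- Statistical methods gives one sample-size calculation, for body weight lost during a marathon: 179 men and 159 women, at 80 % power and two-sided alpha of 0.05.
- Strengths of the study: "Large numbers of participants will allow to discriminate between and, identify associations with, different dietary patterns". No number of runners per diet group is given.

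**The concern.** Telling coaches and runners that a diet is adequate for performance is most naturally heard as saying that runners on it do not perform meaningfully worse. A test whose null hypothesis is no difference cannot deliver that by failing to reject. Non-rejection is also what a small or variable group tends to produce, whatever the true difference.

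Unless vegetarians or vegans turn out significantly faster, the planned tests can give only two answers: a deficit was detected, or it was not. The second answer supports adequacy only when accompanied by an interval showing how large a deficit has been ruled out, and the protocol does not promise one. What is at stake is whether the results can carry the reassurance that the risk–benefit section holds out.

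**Working it through.** **1. The protocol's own sample size.** Inputs from Statistical methods: men 73.9 to 72.2 kg (difference 1.7 kg), SD 8.1 kg; women 59.1 to 57.7 kg (1.4 kg), SD 6.3 kg; 80 % power; two-sided alpha 0.05. With the one-sample (paired) normal formula n = ((1.960 + 0.842) × SD / difference)²:

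- Men: (2.8016 × 8.1 / 1.7)² = 178.2, rounded up to 179.
- Women: (2.8016 × 6.3 / 1.4)² = 158.9, rounded up to 159.

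Both stated figures reproduce. The two-sample formula gives 357 and 318 per group and does not match. The calculation is therefore for a before–after change within runners and says nothing about a contrast between diet groups.

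**2. Precision of the vegan-minus-omnivore difference.** The protocol gives neither diet-group sizes nor an SD of finishing time, so the following rests on assumptions: 338 finishers in total (179 + 159), results in SD units, and a range of group splits. The first split uses the German population shares quoted in Background (10 % vegetarian, 1.1 % vegan). Half-width of the 95 % confidence interval = 1.96 × √(1/n_vegan + 1/n_omnivore).

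| Omnivore / vegetarian / vegan | Calculation | Half-width |
|---|---|---|
| 300 / 34 / 4 | 1.96 × √(1/4 + 1/300) | 0.99 SD |
| 287 / 34 / 17 | 1.96 × √(1/17 + 1/287) | 0.49 SD |
| 236 / 68 / 34 | 1.96 × √(1/34 + 1/236) | 0.36 SD |
| 112 / 113 / 113 | 1.96 × √(1/113 + 1/112) | 0.26 SD |

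Treating everyone who is not vegan as the comparison group at 1.1 % vegans (3.7 against 334.3) gives 1.02 SD, so about 1.0 SD either way. If the observed difference were exactly zero, these half-widths would be the smallest deficits that the data could exclude.

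**3. How often a real deficit would give a non-significant ANOVA.** Same splits, and a true deficit in vegans only of d SD (assumed). The noncentrality parameter is λ = d² × n_vegan × (338 − n_vegan) / 338, with an F test on 2 and 335 degrees of freedom at 0.05.

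| Vegans | d | λ | Chance of non-significance |
|---|---|---|---|
| 4 | 0.5 | 0.99 | 87 % |
| 17 | 0.5 | 4.04 | 58 % |
| 34 | 0.5 | 7.65 | 31 % |
| 113 | 0.5 | 18.8 | 2 % |
| 113 | 0.3 | 6.77 | 36 % |

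The range is wide because the protocol does not fix the group sizes. The table shows that the meaning of a non-significant test depends on those sizes, which is why an interval is needed. It does not show that the study will be imprecise.

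**The case against.** The strongest reply is that the protocol makes no non-inferiority claim. The benefit sentence is hedged. Adequacy is absent from the objectives, outcomes and statistical methods, and every stated aim on performance looks for differences, which analysis of variance and regression suit. The sentence ends by pointing to professional runners. It may therefore mean only that these diets are compatible with running well, which descriptive finishing data could address without any margin. Mean ± standard deviation is a descriptive format and does not forbid intervals for regression coefficients. Limitations of the study already disclaims causal conclusions.

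Much of this stands, and it rules out stronger readings that a reader might infer:

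- That the study sets out to prove adequacy. The text says only that it has the potential to, and the first goal is "to determine potential differences/to identify possible correlations".
- That a non-significant result will be reported as adequacy. No such decision rule is stated.
- That the vegan group will be small. The abstract does expect vegetarians and vegans to be rarer at running events than in the population. But Subjects lists vegetarian nutrition magazines among the recruitment channels, which may enrich the sample, and the total may exceed 338.
- That a non-inferiority margin is required. Imposing one on a comparative cross-sectional survey would be a debatable change of design.

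The mismatch remains. The protocol itself offers the benefit and itself names the analyses, and these do not connect. If adequacy is taken as similarity to omnivores, no group size turns a non-significant difference test alone into evidence for it. The causality disclaimer does not help, because a purely associational statement of similar performance also needs a bound.

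**Conclusion.** The point holds in a limited form. The adequacy benefit is not supported by the analyses as written: they test for differences, are to be summarised as mean ± standard deviation, and have no sample size for the diet contrast. A non-significant diet result would be inconclusive on adequacy. If 338 runners finished, it would leave open deficits of at least about 0.26 SD (equal thirds) to about 1.0 SD (1.1 % vegans), even with an observed difference of zero. Both the total and the splits are assumptions, so these figures give scale and are not a forecast. Because adequacy is one hedged sentence outside the objectives, the weight is modest. The correction is still worth making, because it changes what the study can conclude.

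**What to change.** In Statistical methods, state that the planned regression will report the adjusted vegan-minus-omnivore and vegetarian-minus-omnivore differences in finishing time, as a percentage of the winner's time, with two-sided 95 % confidence intervals. Add that a non-significant diet term will be called inconclusive and not evidence of adequacy.

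Under Evaluation of the risk–benefit ratio, reword the sentence so that the promised conclusion is the estimated difference and its interval. The exception is if the investigators choose to prespecify a margin before analysis; a diet could then be called adequate only if the bound on the slower side excludes that margin. For orientation only, with a true difference of zero, one-sided alpha 0.025 and 80 % power, a margin of 0.3 SD would need 175 runners per group at 1:1, or 96 vegans with 960 omnivores at 1:10.

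The cost is a few sentences, with the same data and model and no extra runners. The downside is that the reassurance may prove unsupportable if the vegan group is small.

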#### Benefits for the subjects

Subjects will not be given any financial compensation. Subjects will receive a brief summary of the results of the NURMI Study if desired.

### Data security

#### IT-team

All data are treated according to appropriate Federal Data Security Laws. The NURMI online surveys hosted on a dedicated virtual server, and run https-only, therefore all relevant data are transmitted SSL-encrypted. Access to the server as well as the file- and database-backups is restricted to the IT staff of the study team and the hosting provider (also a project partner). Security measurements include a local firewall on the server itself, regular security updates of the operating system and applications, no FTP access and no unencrypted access at all. SSH access is restricted to SSH key authentication, ruling out dictionary attacks, automatic detection of dictionary and other brute force attacks against SSH, with automatic locking of attacking clients’ IP addresses, and basic intrusion detection regarding operating system and applications. Gathered data will be stored pseudo-anonymised. Each subject will be assigned an identification code (ID), which will be kept in a separate database. Questionnaire data and subject’s registration data will be stored in different databases. ID linkage will allow us to assign questionnaire data to each subject’s data set. All members of the research staff are bound to their professional obligation to discretion. Data will be used and analyzed exclusively and only in the context of the NURMI Study.

### Trial status

All questionnaires are open and will be accessible through December 31st 2015.

## Abbreviations

NURMI: Nutrition and Running High Mileage
BW: body weight
BMI: body mass index
RPE: rate of perceived exertion
IT: information technology
ID: identification code
